##### Analysing the Effect of Stacked Interventions

We will consider both the effects of single interventions, and the cumulative effects of stacked (multiple) interventions for pregnant women and children in early life. Pathways through the 22 interventions will be identified for target groups (e.g. pregnant teenagers, women with mental health issues, women with no English language skills) and key outcome domains (see Table 3). We will analyse the effect of attending a single intervention and of attending a pathway of stacked interventions. The BSB programme offers a unique opportunity to complete a novel and pragmatic analysis of the impact of stacked interventions for at risk groups of mothers and children.

**Table 3 Tab3:** Additional measurements collected from participants

	Mother		Partner	Baby
	Recruitment	Birth	Recruitment	Birth
Baseline Questionnaire	x		x	
Biological Samples				
Blood	x			
Urine	x			
Cord Blood				x
Saliva			x	
Hair		x		
Anthropometry				
Weight	x		x	x
Height	x		x	
Mid Upper Arm circumference	x			
Triceps skinfold thickness	x			x
Subscapular skinfold thickness				x
Abdominal circumference			x	x
Other Measures				
Carotenoids	x			

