### Sample size

The BiBBS study aims to recruit 5000 babies over 5 years from January 2016 to December 2021. All women booked for delivery at BTHFT are offered an oral glucose tolerance test (GTT) at 26 to 28 weeks gestation. As 75 % of women attend for the GTT [14] the majority of women and their partners will be recruited in these clinics. For those who do not attend, recruitment will take place in community settings (e.g. at midwife appointments) and at other hospital appointments (e.g. diabetes clinics). Although every effort will be made to find and approach all eligible women, we predict reaching approximately 85 % of the eligible population through these methods. We assume, based on analysis of BiB data [14] and BTHFT data, that:1450 babies are born in the BSB area per year,85 % of pregnant women will be reached and invited to take part (75 % at GTT, 10 % in other settings),80 % of these women will agree to take part.In BiB, the ratio of babies to mothers was 1.11, due to multiple births and multiple pregnancies [14].

As such, we expect to recruit 4930 babies and 4440 mothers over a 5 year period.

Uptake for the partners is likely to be lower and we expect, based on achieved recruitment in BiB, to recruit at least 25 % of partners (*n* = 1125).

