**Fig. 2 Fig2:**
[figure not shown]
The recruitment process

Recruitment will be completed by trained researchers who are not involved in the women’s clinical care. Researchers will identify eligible women who have provided assent to data sharing, and will approach women during the GTT clinic to invite them to participate in the cohort. Women who do not attend or who are not approached during the GTT will be approached at another appointment (e.g. community midwife appointments). If this is not possible, the research team will phone to invite them to meet a researcher at a time and place convenient to the woman, for example at an appointment in a local clinic or in their own home. For late presenting women the approach will be when they are an inpatient on the maternity wards.

An anonymised screening log will be maintained to record the woman’s age, ethnicity, language spoken, expected due date, parity, attendance at GTT, and BiBBS status (whether they have been approached, whether they have consented and reason for refusal). This will enable the recruitment of women from all ethnic backgrounds, languages, and age groups to be monitored.

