#### Unique study identifier

Each participant will be allocated a unique identification number which will be used to identify their data throughout the study. Women, their babies and partners will be linked together using a pregnancy identification number. NHS numbers will also be collected for each participant to facilitate data linkage. Families’ attendance at BSB interventions will be tracked using their NHS and UPN numbers. This will allow the cohort to follow families’ journeys through the different interventions. We will use a secure database hosted at the BTHFT to store all of the cohort data on individual children and their parents.

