##### Quasi-experimental design

For most of the BSB interventions, random allocation of families will not be possible, due to ethical and logistical constraints. Quasi-experimental methods will be employed to estimate the causal effects of these BSB interventions. We will consider a range of methods, including propensity scores, regression discontinuity and instrumental variables. Quasi-experimental methods are recommended to evaluate interventions or policy changes in ‘real-world’ circumstances where researchers are not able to manipulate which families receive an intervention [12].

Propensity score approaches can be employed for all interventions that have been taken up by a group within the cohort in order to weight or match a balanced control group. Propensity scores (representing the predicted probability that an individual or family will take part in an intervention, given their baseline characteristics) will be calculated using data collected at baseline. The outcomes for the two groups can then be compared. This approach will allow selection bias to be minimised in the analysis, and the causal effects of interventions to be inferred [23, 24]. For example, for participants of an intervention to support women with mental health problems, propensity scores could be calculated to match a control group of women with similar baseline characteristics including depression and anxiety screening scores, socioeconomic status and ethnicity. Outcomes for women who have taken part in the intervention can then be compared with the matched control group to estimate the intervention effects, for example on maternal mental health, mother-child attachment and child development. However, where factors that predict take-up of interventions have not been identified or accurately measured at baseline, there will be residual differences between groups and remaining concerns about selection biases.

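### The non-randomised comparisons classify families by attendance that builds up over time, with no common start of follow-up, so an ineffective antenatal programme can look protective on outcomes linked to length of pregnancy

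*Protocol article*

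**What the plan says.** The section on stacked interventions sets the contrast: "We will analyse the effect of attending a single intervention and of attending a pathway of stacked interventions". The section on quasi-experimental design forms the exposed group from actual uptake: "Propensity score approaches can be employed for all interventions that have been taken up by a group within the cohort". It then gives the comparison: "Outcomes for women who have taken part in the intervention can then be compared with the matched control group to estimate the intervention effects". Exposure comes from tracking; under the study identifier heading, families' "attendance at BSB interventions will be tracked using their NHS and UPN numbers".

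The propensity scores "will be calculated using data collected at baseline". The same paragraph says that this minimises selection bias and lets causal effects be inferred. Its one caveat concerns predictors of take-up that were not identified, or not measured accurately, at baseline. Timing of take-up is not mentioned.

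Baseline is not one point in pregnancy. The sample size section says that women "are offered an oral glucose tolerance test (GTT) at 26 to 28 weeks gestation", and: "As 75 % of women attend for the GTT [14] the majority of women and their partners will be recruited in these clinics". The recruitment text after Fig. 2 adds: "For late presenting women the approach will be when they are an inpatient on the maternity wards".

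Table 1 lists six antenatal interventions, four that run before and after birth, five postnatal and seven early-years. Some of the last group are for children aged 2, so a pathway can run from pregnancy to that age.

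**The concern.** To be classed as having attended an antenatal course, a woman must still be pregnant when it is held. A woman recruited at 27 weeks who delivers at 31, before her course begins, can only be a non-attender, however willing she was. A woman first approached on the maternity ward had less opportunity to attend, or none. Attenders are therefore guaranteed a stretch of pregnancy that controls are not. This is immortal-time bias.

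The guaranteed time arises after the covariates are measured. Two women with identical baseline scores can still end up in different groups because one delivered early, so a richer baseline data set does not help.

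The outcomes most exposed are those that follow length of pregnancy. Table 3 shows that the baby's weight, skinfolds and abdominal circumference are measured at birth. Random allocation is said to be impossible for most interventions, so non-randomised comparisons will carry most of the evaluation. If the error enters here, each later evaluation may inherit it.

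**Working it through.** **The article's own figures.** Babies: 1450 × 0.85 × 0.80 × 5 = 4930. Mothers: 4930 / 1.11 = 4441, given as 4440. Both reproduce. No effect size, event rate or power is given for the attendance analyses, so everything below rests on assumed inputs, with a true programme effect of zero.

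**1. Preterm birth, simple calculation.** Assumptions: share of recruits delivering before 37 weeks T = 0.08; share delivering before the course can be attended e = 0.015 to 0.025; uptake among the rest u = 0.20 to 0.50. For comparison, Table 1 expects 2500 recipients of the universal antenatal parenting programme, out of 1450 × 5 = 7250 births: 2500 / 7250 = 0.34.

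- Attenders: (T − e) / (1 − e)
- Non-attenders: [(1 − u)(T − e) + e] / [(1 − u)(1 − e) + e]

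| e | u | Attenders | Non-attenders | Risk ratio |
|---|---|---|---|---|
| 0.015 | 0.20 | 6.6% | 8.3% | 0.79 |
| 0.015 | 0.34 | 6.6% | 8.7% | 0.76 |
| 0.025 | 0.34 | 5.6% | 9.2% | 0.62 |
| 0.025 | 0.50 | 5.6% | 10.2% | 0.55 |

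**2. Preterm birth, simulation.** Two million pregnancies, recruitment at week 27, preterm share 5 / 8 / 12%, half of the women willing to attend. The false-positive rate is the chance that comparing two proportions among 4440 mothers declares a difference.

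| Exposure | Null risk ratio | False-positive rate |
|---|---|---|
| One session, weeks 27-38 | 0.55 / 0.55 / 0.56 | at least 0.99 |
| One session, weeks 27-34 | 0.82 / 0.83 / 0.84 | 0.32 / 0.46 / 0.60 |
| Completed course ending weeks 34-39 | 0.17 / 0.18 / 0.19 | 1.00 |

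**3. Same simulation with a common time zero.** Groups fixed at week 27 give 0.99 to 1.01. A week-34 landmark for the one-session exposures (exposure by week 34, women still pregnant) gives 0.99 to 1.00. For a course ending after week 34, nobody has completed by that landmark, so exposure there must be classified by starting the course.

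**4. Later developmental outcome.** Assumed risk 30% after preterm and 15% after term birth, so group risk = 0.15 + 0.15 × preterm share.

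- Inputs of step 1, mildest: (0.15 + 0.15 × 0.066) / (0.15 + 0.15 × 0.083) = 0.98. Most extreme: (0.15 + 0.15 × 0.056) / (0.15 + 0.15 × 0.102) = 0.96.
- Giving births before the course three times the term risk (45%) moves the most extreme case to 0.92.
- Completed course ending weeks 34-39: 0.93 / 0.90 / 0.87.

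**5. Leaving the area.** Assumptions: 5-20% leave, half of them before they could attend; uptake 30%; outcome risk 20% in stayers. If leavers have the same risk as stayers, or are not linked, the null risk ratio is about 1.00. If leavers have twice the risk and remain linked, it is 0.97, 0.94 and 0.90 for 5, 10 and 20% leaving.

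**The case against.** **This is a condensed article.** It speaks of methods that may be considered, and its discussion says that evaluations will be developed as each intervention is designed. Nothing in it forbids risk-set matching. That stands as far as it goes: an unstated time zero alone would not be a finding. But the article does state an attendance contrast, a score built on baseline data and a causal claim for that combination. Applied as written, they give the bias shown.

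**The largest figures use preterm birth.** The visible text does not name it as an outcome. The named domains are social and emotional development, language, and nutrition and obesity; the matching example uses maternal mental health, attachment and child development. This stands and limits the size of the point. Birth weight and skinfolds are nevertheless collected, and they depend on gestation.

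**The timing is assumed.** Midwives give information on the programme at about 10-12 weeks, so continuous midwifery or the phone app could begin well before the glucose test. For those, few women would deliver before they could take part. This also stands; the 1.5-2.5% has no source in the article.

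**Stronger readings the article does not support.** A reader might infer that every family whose pregnancy or stay was cut short becomes a control, and that any useless programme will therefore look protective. But miscarriages, stillbirths and child deaths lead to withdrawal, so the misplacement concerns early live births. Women planning to move before the birth are excluded, and later leaving biases the result only under the conditions in step 5. Twelve of the 22 interventions start after birth, when gestation is already known and can be adjusted for. A reader might also infer that the bias grows with each stacked intervention. The article describes pathways for target groups, not a count-based dose-response, and that growth has not been quantified.

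The article does acknowledge residual selection bias and the difficulty of finding comparable controls, but neither remark concerns timing.

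**Conclusion.** The point holds for the non-randomised attendance comparisons of antenatal interventions and of pathways that include them. Exposure depends on attendance over time, adjustment uses recruitment data only, and no common start of follow-up is tied to exposure. A null programme can then look protective on outcomes linked to length of pregnancy, however complete the baseline data.

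The size depends on the outcome: a null risk ratio of 0.55-0.79 for preterm birth under the simple assumptions, but only about 0.87-0.98 for later developmental outcomes, with the lower end needing a completed course that ends near term. For length of stay the bias is conditional: 0.90-0.97 if leavers have twice the risk and stay linked, otherwise about none. These ranges rest on assumed preterm shares, session timing, uptake and outcome risks. They show what can happen, not what will.

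The randomised TwiCs are not affected, nor is regression discontinuity with groups set by the cut-off. The change should be made because it is cheap and because the stated causal claim does not cover this bias.

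**What to change.** In the sections on quasi-experimental design and on stacked interventions, state that eligibility, exposure classification and start of follow-up are set at the same time point, by one of two routes:

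- **Risk-set matching.** When a recipient enters the intervention, draw controls from families who at that gestational or child age are still pregnant (or have a living child), resident and eligible. Follow both from that time.
- **Landmark.** Fix a gestational or child age, classify exposure by the interventions started by then, keep only families still eligible at that age, and analyse only later outcomes. This suits stacked pathways best.

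For postnatal interventions, adjust for gestation at birth. Limit the causal claim to comparisons aligned in this way, and add timing of take-up to the stated limitations.

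The cost is wording and use of the attendance already tracked, provided that its dates are kept. Families with an event before the landmark leave that comparison. In the simulation the share delivered before week 34 is the preterm share × exp(−3/2.5) = preterm share × 0.30, or 1.5% to 3.6% of women for preterm shares of 5% to 12%, so the loss of sample is slight.

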##### Process Evaluation / Monitoring and Fidelity

The cohort will also facilitate on-going quality improvement for BSB interventions. On-going measurement and monitoring of intervention uptake and outcomes will enable learning and adaptation of interventions to ensure that they are widely used and effective. A separate protocol will be written for the process evaluation, which will follow Medical Research Council (MRC) guidance [27], incorporating the Conceptual Framework for Implementation Fidelity [28].

### Project management

The success of BiBBS is dependent upon input from a wide range of people, organisations and academic partners. The cohort will be managed and monitored using the same management structure established for the BiB cohort [16] and the groups established for BSB (e.g. Partnership board and the CRAG). Full details of the management structure can be seen in Additional file 1.

### Data sharing

The BiBBS experimental cohort study will enable the evaluation of the BSB interventions and increase understanding about how to improve health and development in inner city Bradford. It will contribute knowledge and understanding about the effects of prenatal and child interventions, and the causes of disease that will have international relevance. The BiBBS cohort also offers a platform to develop and test new early childhood interventions, and conduct research projects in a diverse population. Researchers with relevant proposals are encouraged to visit the BiB website (www.borninbradford.nhs.uk) to find out more about the application and selection process.

In addition, data and samples collected throughout the course of the cohort will be available to external researchers and proposals for collaboration will be welcomed. Until recruitment is complete, and all routine outcome measures have been linked and data cleaned, such access may be limited. Researchers with proposals to use the cohort data should complete an outline data request pro forma available on the BiB website (www.borninbradford.nhs.uk).

## Discussion

The BiBBS study builds on the success and momentum of the BiB birth cohort study which recruited over 13,500 babies born across the city between 2007 and 2011 and has developed internationally-leading experience in the administration and collection of data and community relationships [14, 16].

Birth cohorts are prospective, longitudinal epidemiological studies which provide some of the most robust evidence of associations between early life exposures and later outcomes of health and well-being. They can help identify modifiable risk factors that can be targeted in subsequent interventions. However they have not previously been set up to test whether interventions are effective. The focus of the BiBBS cohort is on intervention rather than observation. As far as we are aware, no other birth cohorts have used this design, making BiBBS the world’s first such experimental birth cohort study.

Many risk factors for adverse health and well-being outcomes in children are already well described: parental lifestyle factors such as smoking; child lifestyle factors such as diet and physical activity; family functioning such as parenting practices; health service access; environmental factors such as air pollution [4, 5]. The crucial research goal is to find better ways of changing behaviours and environments to promote positive health and protect against harmful exposures.

BSB provides a £49 million natural experiment to inform public health policy and practice. Our novel experimental birth cohort design has the potential to help provide timely evidence of effectiveness of multiple interventions, a situation that has changed little in the 14 years since the Wanless report identified an “almost complete lack of an evidence base on the cost-effectiveness of public health interventions” [29]. When the proposal for BSB was developed, we were surprised by the poor quality of evidence available for early life interventions. Of the 22 interventions only two were evidence based (tested and proven effective using robust study designs). Since then, one of the two has been found to be ineffective in the UK [30]. This uncertainty highlights the importance of building in robust evaluation to BSB. Over the next 10 years we will be able to address this uncertainty and add to our knowledge base on early life interventions.

The evaluation of complex interventions is challenging. RCTs are considered to be the gold standard, however they are not always feasible or ethical, are time consuming and expensive, and findings don’t always translate across different contexts. For example the Family Nurse Partnership programme had benefits for birth weight, maternal smoking, inter-pregnancy interval and infant hospital admissions in RCTs in the US, but these benefits were not seen in a recent UK trial [30–33]. The natural BSB experiment provides a unique opportunity to evaluate the effects of multiple, individual interventions on child outcomes using TwiCs where it is ethical and feasible to randomly allocate families to interventions, and other approaches, including quasi-experimental methods where interventions are not randomised. The collective effects of stacked interventions on child outcomes will also be assessed. This design will be efficient both in terms of time and costs of evaluation as well as providing a ‘real world’ evaluation of the cumulative effect of multiple interventions. The use of routine health and education data linkage will provide large scale, efficient and timely outcomes that are relevant to practice and policy.

We acknowledge the uncertainties associated with this experimental cohort design. The commissioning and design of the interventions are out of our control, and our key challenge is to be flexible and adapt our choice of evaluation methods to the interventions as they are designed. The evaluations can only be developed as each intervention is designed and we plan an iterative process for this. We recognise potential limitations in internal validity, including identifying a comparable control group, and our aim is to minimise these biases through collection of detailed baseline data and use of quasi-experimental methods to estimate causal effects. This efficient evaluation of interventions as they are implemented within the BSB programme will support the understanding of effectiveness of multiple interventions. The evidence of effectiveness of these interventions is likely to be generalizable to other deprived, multi-ethnic urban populations.

Over the last 10 years we have developed considerable expertise in the birth cohort design, implementation and analysis with BiB. A key reflection over this period is that while the risk factors for adverse health and social outcomes are increasingly well described, the solutions to tackling them remain as elusive as ever. The BiBBS experimental birth cohort study can contribute much needed evidence to inform policy makers and practitioners about effective approaches to improve health and well-being for future generations.

## Abbreviations

BiB, Born in Bradford; BiBBS, Born in Bradford’s Better Start; BSB, Better Start Bradford; BTHFT, Bradford Teaching Hospitals NHS Foundation Trust; CRAG, Community Representatives Advisory Group; GCP, Good Clinical Practice; GTT, Glucose Tolerance Test; MRC, Medical Research Council; RCT, Randomised Controlled Trial; TwiCs, Trials within Cohorts; UPN, Unique Pupil Number
